## Abstract

*Helicobacter pylori* (Hp) infects half of the world population and is responsible for gastric, duodenal ulcers and gastric cancer. The eradication of Hp cures ulcers and prevents ulcer recurrences and gastric cancer. Antibiotic resistance of Hp, and particularly clarithromycin resistance, is the primary cause of treatment failure and is a major concern identified by the WHO as a high priority requiring research into new strategies. Treatments guided by the detection of antibiotic resistance have proven their medical and economical superiority. However, this strategy is severely hampered by the invasive nature of the fibroscopy, since antibiotic resistance detection requires gastric biopsies. The eradication of Hp involves primary care physicians. The objective of this study will be to evaluate the feasibility of a strategy for the management of Hp infection in primary care by a recently developed non-invasive procedure and its non-inferiority in eradication rates compared with the strategy recommended by the French National Authority of Health. The non-invasive procedure is a PCR on stool to detect Hp infection and mutations conferring resistance to clarithromycin allowing a treatment guided by the results of the PCR. We present the protocol of a prospective, multicenter, randomized, controlled interventional study in two arms.

## 1. Introduction

*Helicobacter pylori* (Hp) infection is the most common chronic bacterial infection in the world (50% of the world population, 20 to 30% of the French population) [1,2,3]. Acquired in childhood, most often within the family, this infection persists throughout the individual’s life in the absence of specific treatment [4]. Many infected persons present chronic gastritis, most of the time asymptomatic. Only 5–10% of infected people will develop a gastric or duodenal ulcer, 1–3% gastric cancer (adenocarcinoma or MALT lymphoma) [5]. This represents 80,000 cases of peptic ulcers and 6000 gastric cancers (5-year survival rate of 20%) in France each year [6,7]. Hp is recognized as a class 1 carcinogen by the WHO (800,000 deaths from gastric cancer worldwide each year) [7,8]. Treatment cures peptic ulcers and prevents their recurrence, prevents gastric adenocarcinoma and cures MALT lymphoma without associated translocation. Resistance to the antibiotics used in eradication therapy is the primary cause of treatment failure, followed by poor compliance [9,10].

In Europe *H. pylori* resistance rates in 2018 (on 1211 strains) were 21.4% for clarithromycin, 15.8% for levofloxacin and 38.9% for metronidazole. Prevalence was significantly higher in Central/Western and Southern than in the Northern European countries [11]. In the same year, 20.9% of Hp strains in France were resistant to clarithromycin, 17.6% to levofloxacin, and 58.6% to metronidazole [10,12,13]. The 2017 recommendations of the French National Authority for Health (Haute Autorité de Santé, HAS) placed “guided” and “empirical” treatment modalities at the heart of strategies for Hp eradication [14]. These “guided” treatments following the identification of resistance to certain antibiotics have proven their medico- economic superiority in the eradication of this bacterium [15]. This guided treatment strategy requires gastric biopsies and culture of this difficult-to-culture bacterium and/or a real-time PCR [16,17]. This strategy is severely hampered by the invasive nature of the gastroscopy, the difficulty of the culture and the cost of the PCR. It has been widely demonstrated that treatment guided by resistance detection is more effective, less expensive and better tolerated. The World Health Organization, WHO, has identified Hp resistance to clarithromycin as a high priority requiring research into new strategies. In France, guided treatment represents less than 1% of eradication treatments (Longitudinal Patient Data and French national Health information system, SNIIRAM), despite the recommendations of the HAS and the European and French Societies for Gastroenterology to favor treatment guided by the results of Antibiotic Susceptibility Testing, AST, or PCR.

Serology, a non-invasive test, easy-to-perform and inexpensive, has demonstrated good performances (sensitivity, Sen, over 96% and specificity, Spe, between 60 and 90%). However, it does not allow detection of antibiotic resistance and the active nature of the infection. Similarly, other non-invasive tests have been developed to detect Hp in other, less invasive specimens, such as respiratory specimens (for the urea breath test, used for eradication testing) or stool (stool antigen test) (described or reviewed in refs. [18,19,20,21]). The latter have the same limitations as serology, being limited to the presence/absence of Hp without any precision on the AST profile, crucial for disease management in many countries of the world. Several diagnostic companies have recently marketed PCR kits for the detection of Hp infection and clarithromycin resistance mutations in stool. The performances of the Amplidiag *H. pylori* + ClariR test (Mobidiag, Hologic Inc., Marlborough, MA, USA) for detection of Hp infection and detection of clarithromycin resistance by real-time PCR have been demonstrated [10]. These excellent performances (Sen 96.3% and Spe 98.7%) make it possible to consider using this non-invasive technique for diagnosis and treatment orientation and consequently to be able to carry out guided treatment without recourse to gastro-duodenal endoscopy and biopsies. PCR testing of stool for Hp infection and resistance to clarithromycin is simple and requires few trained personnel. Its non- invasive character may allow it to be used in patients with an indication for the detection and treatment of Hp infection and without an indication for gastro-duodenal endoscopy.

The eradication of Hp strongly involves primary care physicians (general practitioners, GPs). The diagnosis of Hp infections in the general population requires close collaboration between primary care physicians and other specialists (gastroenterologists, pathologists, bacteriologists...). In France, it has been estimated that GPs see almost the entire population of France in their offices at least once a year. Given the prevalence and incidence of Hp, their role is becoming increasingly important [22]. The present project is therefore related to a field problem. The GP’s skills in the prevention of gastric cancer and pathologies of the upper digestive tract are an integral part of the discipline’s professional reference system [23].

The main objective of this study will be to evaluate, in a real-life situation, the feasibility of a strategy for the management of Hp infection by a non-invasive procedure in primary care and its non-inferiority in eradication rate compared with the strategy recommended by the HAS using a combination of serology and endoscopy. The secondary objectives of this study will be: to evaluate the adherence of patients to the care pathway (compliance to endoscopy, treatment, stool collection, serology); to evaluate the follow-up of recommendations in the management of Hp infections by health professionals (GPs and gastroenterologists) (e.g., empirical/guided treatment, evaluation of pre-neoplastic lesions); to validate, in real-life circumstances, real-time PCR in stool in comparison with serology in primary diagnosis and with urea breath test in eradication control.

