### 2.3. Study Outcomes

**Primary endpoint.** The primary endpoint will be an assessment of the cure rate through the results of a urea breath test performed 6 weeks after the end of treatment (proof of Hp eradication).

**Secondary endpoints.** The secondary endpoints will be assessment of: (i) the number of guided treatments (depending on the real-life application of the French authorities recommendations); (ii) the number of endoscopies (estimating the number of endoscopies avoided due to the optimized process); (iii) the number of biopsies at endoscopy; (iv) the number of patients who refused endoscopy after serology or positive PCR or did not follow-up after referral to the gastroenterologist; (v) the number of treatment side-effects and treatment dropouts; (vi) the discordance rate between real-time PCR tests in stool and serology in primary diagnosis; (vii) the discordance rate between real-time PCR tests in stool/breathing test in eradication control; and (viii) cure rate assessed by the result of a urea breath test performed 6 weeks after the end of treatment (proof of Hp eradication) depending on the antibiotic susceptibility testing identified at diagnostic.

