### 2.5. Statistical Analysis

**Sample size calculation.** Assuming 20% prevalence in source population, and based on a one-sided hypothesis, 100 patients will be included in each strategy arm to demonstrate a 15% difference between each strategy with statistical risks at 5% (type I error, α) and 15% (type II error, β). We are planning to enroll 1000 patients to consider a maximum patient loss of 10%. Considering that each investigator involved in the HepyPrim study follows more than 1200 patients each year, the inclusion objective was set to 50 patients per investigator and the number of investigators was set to 20. These investigators have been selected in the newly constituted “physicians’ network for research in New Aquitaine”.

**Analysis.** The data will be analyzed blindly on an intention-to-treat basis, assuming a non-inferiority hypothesis. No interim analysis is planned. A per protocol analysis will be performed as a secondary sensitivity analysis. Quantitative variables will be described by their mean and standard deviation or median and interquartile range according to the normality of the distribution. Categorical variables will be described by their number and percentage. Continuous variables will be compared by a Student’s *t*-test or Mann–Whitney U-test according to the normality of the distribution. Categorical variables will be compared by a chi-square test or Fisher’s exact test. The tests will be analyzed using GraphPad Prism version 9.0 (GraphPad Software, San Diego, CA, USA). A significant difference will be retained for a *p*-value < 0.05. All tests will be two-tailed, stratified by center and for multiple comparisons if appropriate.

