Moreover, this is the first study to enable the structuring of a research network in primary care in Poitou-Charentes. This project is the first of this network, which will be made up of 20 co-investigators, all of whom are GPs. Others were identified during the recruitment phase carried out as part of a thesis on the practice of general medicine by two interns in general medicine. This project is therefore founding and structuring for a primary care research network.

This study may allow evaluation of the performance of PCR in stools in comparison with the combination of serology/pathology/bacteriology for the initial diagnosis, evaluation of the performance of PCR in stools in comparison to the respiratory test for the control of eradication. Moreover, it may lead to the constitution of a biobank of stools of infected patients, in view of further study of the development of in vitro diagnosis.

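### Overall PCR-serology discordance cannot validate stool PCR at primary diagnosis: on the protocol's own figures even a perfect PCR would disagree with serology in about 9% to 33% of patients, and no listed endpoint compares PCR with biopsy.

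*Protocol article*

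**What the plan says.** In section 1 (Introduction), the secondary objectives include "to validate, in real-life circumstances, real-time PCR in stool in comparison with serology in primary diagnosis". The second half of that objective, eradication control, uses the urea breath test and is not at issue here.

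In section 2.3 (Study Outcomes), secondary endpoint (vi) is "the discordance rate between real-time PCR tests in stool and serology in primary diagnosis". It has no agreement threshold, and discordant pairs are not resolved by a third test. No endpoint in that list compares PCR with biopsy.

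On serology, the Introduction reports good performance ("sensitivity, Sen, over 96% and specificity, Spe, between 60 and 90" percent), but adds that "it does not allow detection of antibiotic resistance and the active nature of the infection". For the PCR it gives sensitivity 96.3% and specificity 98.7%.

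Section 2.1 (Control group) uses serology only to select patients for gastroscopy. Histology and/or bacteriology on the biopsies then decides whether infection is present. Control patients also supply a stool sample, whose PCR result is withheld until the end of the study.

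Section 3 (Discussion) says that PCR performance may be evaluated "in comparison with the combination of serology/pathology/bacteriology for the initial diagnosis".

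**The concern.** The objective is about the accuracy of PCR, but the endpoint is raw disagreement with a test that, by the protocol's account, cannot show active infection and may be falsely positive in 10% to 40% of uninfected patients. When four in five patients are uninfected, those false positives dominate the disagreement. A high rate could then discredit a good PCR, and a moderate rate could be read as validation without supporting it.

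The question matters because PCR alone decides treatment in the intervention arm. Section 2.1 also notes that the kit was developed for gastric biopsies, so its performance on self-collected, mailed stool is a real question for this trial. The comparator named in the Discussion would address it better, but it does not appear among the endpoints.

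**Working it through.** The protocol states no expected discordance, so there is no figure of its own to reproduce. The check asks what endpoint (vi) would show under the protocol's own inputs.

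**Inputs**
- Prevalence: 20% (section 2.5, "Assuming 20% prevalence in source population"). 30% is used as a second value (Introduction, "20 to 30% of the French population"). Prevalence among patients with an indication for testing is not given.
- Serology: sensitivity 96% (the lower bound of the stated figure), specificity 60% to 90%.
- PCR: either perfect, or 96.3% sensitive and 98.7% specific as stated.
- Assumption: test errors are independent given infection status.

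**1. Perfect PCR.** Discordance = prev × (1 − Sen_sero) + (1 − prev) × (1 − Spe_sero).
- 20% prevalence, specificity 90%: 0.2 × 0.04 + 0.8 × 0.10 = 8.8%.
- 20% prevalence, specificity 60%: 0.2 × 0.04 + 0.8 × 0.40 = 32.8%.
- 30% prevalence: 0.3 × 0.04 + 0.7 × 0.10 = 8.2%, and 0.3 × 0.04 + 0.7 × 0.40 = 29.2%.

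**2. PCR as stated, 20% prevalence.** Discordance = prev × [Sen_P(1 − Sen_S) + (1 − Sen_P)Sen_S] + (1 − prev) × [Spe_P(1 − Spe_S) + (1 − Spe_P)Spe_S].
- Infected part: 0.2 × (0.963 × 0.04 + 0.037 × 0.96) = 0.0148.
- Specificity 90%: 0.0148 + 0.8 × (0.987 × 0.10 + 0.013 × 0.90) = 10.3%.
- Specificity 60%: 0.0148 + 0.8 × (0.987 × 0.40 + 0.013 × 0.60) = 33.7%.

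The stated PCR errors therefore add 1.5 points (specificity 90%) or 0.9 points (60%). The uncertainty in serology specificity moves the endpoint by 32.8 − 8.8 = 24 points.

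**3. Can the rate rank a poor PCR below a perfect one?** Take a PCR that misses half of all infections (an assumption), with specificity 98.7% and serology specificity 90%: 0.2 × (0.5 × 0.04 + 0.5 × 0.96) + 0.8 × 0.1104 = 18.8%. That is below the 32.8% of a perfect PCR read against serology of 60% specificity. At 30% prevalence the order is the same: 22.7% against 29.2%.

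**4. Serology used as the reference for PCR sensitivity.** Seropositive fraction at 20% prevalence: 0.192 + 0.08 = 0.272 (specificity 90%) or 0.192 + 0.32 = 0.512 (60%). A perfect PCR would appear to have sensitivity 0.192/0.272 = 70.6% or 0.192/0.512 = 37.5%.

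**5. What the seronegative patients show.** The infected share among them is 0.008/0.728 = 1.1% (specificity 90%) or 0.008/0.488 = 1.6% (60%). A perfect PCR would be positive in only that share. With PCR specificity of 90% (an assumption), about 11% would be positive: (0.008 × 0.963 + 0.72 × 0.10)/0.728 = 10.9%, or (0.008 × 0.963 + 0.48 × 0.10)/0.488 = 11.4%. This cell does inform PCR specificity.

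**6. Patients available for a biopsy comparison.** Assume 500 control patients (half of 1000) and 60% to 90% endoscopy completion, a range not in the documents.
- Seropositive: 500 × 0.272 = 136 to 500 × 0.512 = 256.
- Biopsied: 136 × 0.6 = 82 to 256 × 0.9 = 230.
- Infected among them: 500 × 0.2 × 0.96 = 96, giving 96 × 0.6 = 58 to 96 × 0.9 = 86.

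The 10% patient loss in section 2.5 is not applied; it would lower these counts.

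**The case against.** The strongest reply is that endpoint (vi) is a legitimate agreement measure. It does not call serology a gold standard and sets no pass mark. Serology also opens the control pathway, so its disagreement with PCR is relevant to comparing the strategies. That stands: the endpoint should be kept, and the defect lies in asking it to validate PCR.

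Second, a reader might infer that discordance carries no information about PCR at all. The documents do not support this. Step 5 shows that poor PCR specificity would appear among seronegative patients. The overall rate also moves if PCR performs well below its stated figures: with serology specificity 90%, PCR sensitivity of 70% would give 15.2% and PCR specificity of 90% would give 15.9%, against 10.3%. With serology specificity 60%, however, the same loss of PCR specificity adds only about 1.4 points.

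Third, a reader might infer that the protocol itself calls serology unspecific. It does not: it calls the performance good and quotes the range. The limitation that it states is about active infection and resistance.

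Fourth, the Discussion announces a wider comparison, and a condensed article may leave its tabulation to the analysis plan. That is fair as to method. But the article lists its secondary endpoints, and the one tied to this objective names serology alone, so the two sections do not match.

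Fifth, biopsy is not a complete reference. It follows only a positive serology, seronegative patients are never verified at diagnosis, and bacteriology is done only where available. This stands and limits what the fix can claim.

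**Conclusion.** The point holds in a bounded form. Overall PCR-serology discordance cannot deliver the stated objective of validating stool PCR at primary diagnosis, and in particular gives no clean estimate of PCR sensitivity. A perfect PCR would show about 9% to 33% discordance at 20% prevalence (8% to 29% at 30%), and the stated PCR errors change this by only 0.9 to 1.5 points. These figures rest on 96% serology sensitivity, independent errors and a source-population prevalence that may not match the enrolled patients; the conclusion is the same at both prevalences.

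The seronegative, PCR-positive cell remains informative about specificity. The finding concerns half of one secondary objective. It does not touch the primary endpoint, the sample size or the breath-test comparison.

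**What to change.** 1. Add a secondary endpoint in control-arm patients who have endoscopy: sensitivity and specificity of the baseline stool PCR against the biopsy result (positive if histology and/or bacteriology is positive, where available), with exact 95% confidence intervals. State that it applies to seropositive patients only. This also brings the endpoint list into line with the Discussion.
2. Keep PCR-serology discordance as descriptive agreement, reported separately as PCR-positive/serology-negative and PCR-negative/serology-positive, and stop describing it as validation.
3. Confirm that biopsy bacteriology is captured. Section 2.4 lists histopathology for the control group but does not name bacteriology.

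The cost is a small extra analysis on stool samples and biopsies already planned, with no new procedure for patients. The drawbacks are limited precision (about 82 to 230 patients, of whom about 58 to 86 are infected, on the assumptions in the working) and no biopsy verification in seronegative patients.

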## 2. Methods

### 2.1. Trial Design and Setting 

This study will be a prospective, multicenter, randomized, controlled interventional study in two arms (Figure 1). Randomization will be carried out through a secure web-based randomization system and stratified by center (i.e., each investigator). The duration of the inclusion period will be 12 months. The participation period for each participant will be 4 months for a total study duration of 16 months (twelve months of inclusion plus four months of follow-up for the last included patient).

A computer-generated block-randomization sequence using permuted-block randomization of varying block sizes will be performed by the statistician and will be carried out via Ennov System software. The statistician will not be involved in either screening the patients or assessing outcomes. The randomization process will be accessible to all physicians working in the emergency department through user personal identification logins to access the website (https://chu-poitiers.hugo-online.fr/CSOnline/, accessed on 27 December 2021). It will become effective following confirmation of inclusion and exclusion criteria. Thereafter, patients will be assigned to one of the two study groups (in a 1:1 randomization scheme) according to the strategy (described thereafter).

**Intervention group.** Patients randomized to the Intervention group (new strategy arm) will receive a prescription for Hp serology with instructions for the laboratory to limit the communication of the results to the physician alone and a stool self-sampling kit (containing instructions, biodegradable basket to be placed on the toilet, e-Nat tube (Copan, Italia), and stamped envelope for mailing to the laboratory). After centrifugation, 400 μL of the eNAT tube supernatant will be extracted using the NucliSENS easyMAG system (bioMérieux, Marcy-l’Étoile, France), according to the manufacturer’s instructions, in 2 mL lysis buffer under the following conditions: the specific B 2.1 protocol with 140 μL of silica, after adding 1 μL of internal control (Amplidiag Easy Process Control I; Mobidiag, Hologic inc.), for a final volume of eluate of 70 μL. Nucleic acid will then be amplified using the Amplidiag *H. pylori* + ClariR test assay. This test, the only one that will be considered for this arm, consisting in a multiplex PCR, will obtain three different results (negative/absence of detection of *Helicobacter pylori* or detection of *Helicobacter pylori* or detection of *Helicobacter pylori* associated with mutation implicated in clarithromycin-resistance, i.e., A2142C, A2142G and A2143G). Originally developed for detection in gastric biopsy this kit may give appropriate results in stool samples [10,24]. According to the results of their biological assay, patients will be seen by their investigator within six weeks to either initiate or not initiate eradication therapy, i.e., a positive test will determine Hp infection and indication for treatment. The absence of detection of a clarithromycin-resistant strain will allow prescription of a guided treatment combining PPI, amoxicillin, and clarithromycin for 10 days according to the HAS recommendations. According to the same recommendations, the detection of a clarithromycin-resistant strain will allow prescription of a guided treatment combining PPI, amoxicillin, and metronidazole or quinolone for 10 days. At least 4 weeks after stopping antibiotics (and at least 2 weeks after stopping PPIs), an eradication control will be carried out using a respiratory test (urea breath test), concomitant to the collection of a stool sample for retrospective analysis by real-time PCR. A negative breath test will define the success of the treatment, while a positive test will define treatment failure. The latter will be managed in the usual manner by the GPs in charge of the patient. At the end of the follow-up, infected (positive for serology and/or PCR assays) and treated patients over 45 years of age will be referred to a gastroenterologist for gastric biopsies for histological analysis of the gastric mucosa for pre-neoplastic and cancerous lesions.

**Control group.** Patients randomized to the reference strategy control group (HAS strategy arm) will receive a prescription for Hp serology and a stool self-sampling kit (instructions, biodegradable basket to be placed on the toilet seat, E-Nat tube (Copan), swab, stamped envelope for mailing to the laboratory). Only the serology result will be considered for this arm (to avoid any deviation from the protocol, results of other tests will not be communicated before the end of the study). According to the results of their biological assay, patients will be seen by their investigator within six weeks. A positive serological test will lead to a gastroscopy with biopsies for histology/pathological and bacteriological analysis if available. Each person referred will be accompanied by the “request for gastroscopy in case of positive Hp serology” letter, according to the HAS model. These anatomopathological and/or bacteriological analyses will determine the presence of a Hp infection, if bacteria suggestive of Hp are observed in pathological examination and/or if the conventional and/or molecular biology are positive from gastric biopsies sent to bacteriology laboratories. An infection will determine the indication for treatment, either empirically, in the absence of an antibiogram or PCR result (bismuth or concomitant quadritherapy), or guided by the results of the AST or culture according to HAS recommendations (pertinence of care sheet). At least 4 weeks after stopping antibiotics (and at least 2 weeks after stopping PPIs), an eradication control will be carried out using a respiratory test (urea breath test), concomitant to collection of a stool sample for retrospective analysis by PCR. A negative breath test will define the success of the treatment, while a positive test will define treatment failure. The latter will be managed in the usual manner by the GPs in charge of the patient.

It should be noted that for ethical and regulatory considerations, it was decided, after the collection of results (at the end of the study for each patient), to give out the results of these analyses (urea breath test, serology, PCR before/after treatment) in order to allow the general practitioner to manage the patient in an appropriate manner.

